**Criteria for developing CRS**

One or more of the following criteria present*

C-reactive protein > 100 or > 50 mg/L but doubled in the past 48 hours

Lymphocyte count < 0.6 x 109/L

Serum Interleukin-6 (IL-6) ≥ 3x upper normal limit

Ferritin > 300 ug/L (or surrogate) with doubling within 24 hours

Ferritin > 600 ug/L at presentation and Lactate dehydrogenase >250 U/L

Elevated D-dimer (> 1 mcg/mL)

*We defined low risk for developing CRS as the presence of 1 criterion; moderate risk if two to three criteria; high risk if ≥ 3 criteria*

**Exclusion criteria**

Negative RT-PCR test for SARS-CoV-2 Mild symptoms not requiring ICU admission

Terminally ill patient who are receiving palliative care History of allergy to TPE and its products

**TPE mode and therapeutic considerations**

A dose of 1.5 plasma volume exchanges will be used for the first dose then 1 plasma volume exchange on alternate days or daily for a total of 5-7 doses per individual clinical case scenario. Spectra Optia ^TM^ Apheresis System operates with acid-citrate dextrose anticoagulant (ACDA) as per Kidney Disease Improving Global Outcomes (KDIGO) 2019 guidelines. The plasma will be replaced with albumin 5% or fresh frozen plasma (in patients with coagulopathy). It is well documented that TPE removes various medications i.e., monoclonal autoantibodies; hence, use of Tocilizumab, steroids or other drugs as co-interventions will be not applied in our study group receiving TPE. The latter will not remove IgM molecules as they are too large. It appears that the therapy is more focused on controlling the inflammatory response by removing cytokines as per US FDA recommendations. [22]

**TPE technical details and infrastructure** TPE will be initiated using the Spectra Optia ^TM^ Apheresis System equipped with the Depuro D2000 Adsorption Cartridge (Terumo BCT Inc., USA). Sessions will be performed per US FDA recommendations for 4 hours per day to discreetly reduce the cytokine cascade. The number of sessions will be individualized according to pertinent clinical and laboratory parameters (i.e., improvement of P/F ratio, reduction of ferritin, IL-6 and LDH levels). Current US FDA recommendations state that: 1. SARS-CoV-2, the virus that causes COVID-19, can cause a serious or life-threatening disease or condition, including severe respiratory illness, to humans infected by this virus;

2. Based on the totality of scientific evidence available to FDA, it is reasonable to believe that the Spectra Optia Apheresis System with the Depuro D2000 Adsorption Cartridge may be effective in treating patients 18 years of age or older with confirmed COVID-19 admitted to the ICU with confirmed or imminent respiratory failure, and that the known and potential benefits of the Spectra Optia Apheresis System with the Depuro D2000 Adsorption Cartridge, when used to treat COVID-19 patients 18 years of age or older, outweigh the known and potential risks of the Spectra Optia Apheresis System with the Depuro D2000 Adsorption Cartridge; and

3. There is no adequate, approved, and available alternative to the emergency use of the Spectra Optia Apheresis System with the Depuro D2000 Adsorption Cartridge for the treatment of these COVID-19 patients.

The Spectra Optia Apheresis System with the Depuro D2000 Adsorption Cartridge devices mechanisms of function are as follows:

The D2000 Adsorption Cartridge operates in conjunction with the Terumo Spectra Optia device. The D2000 Adsorption Cartridge is integrated into the extracorporeal circuit, downstream from where the plasma is separated, into the Secondary Plasma Device (SPD) position of the circuit. After priming the D2000 Adsorption Cartridge and assembling the inlet and outlet lines to the plasma circuit, plasma filtration can be run for up to 4 hours, to be repeated as needed. The D2000 Adsorption Cartridge contains activated uncoated coconut shell (carbon granules) charcoal (100 gm), and the nonionic resins Amberlite XAD-7HP and Amberchrom GC300C. These adsorption materials have been demonstrated to be efficacious in the removal of statistically significant proportions of IL-3, IFN-gamma, IL-10, IL-1B, IL-6, IL-8, MCP-1, and TNF-alpha when compared to control. The adsorbents attract solutes through a variety of forces, including hydrophobic interactions, ionic (or electrostatic) attraction, hydrogen bonding, and van der Waals interactions. Management of the CRS associated with COVID-19 whilst treating the underlying pathogenesis may decrease patient morbidity. The reduction of cytokines must be done in a discrete, controlled fashion, to balance the patient’s immune response to the infection with the removal of the excess inflammatory cascade. Therefore, therapy with the D2000 will be administered for up to 4 hours per day. The Spectra Optia® Apheresis System Equipment (61000) is a non-patient, non-fluid contacting device. The following device settings have been validated for operation of the D2000 Adsorption Cartridge with the Terumo Spectra Optia with SPD software:

Prime divert volume: 200 mL

Notification pressure limit: 200 mmHg

Maximum pressure limit: 300 mmHg

Maximum plasma flow rate: 50 mL/min

Prime can be performed at up to 100 mL/min. At the start of treatment, the plasma pump flow rate may be adjusted up to 25 mL/min for the first 250 mL of plasma processed. Then, the plasma flow rate may be increased up to 50 mL/min as needed. This may be managed by the physician to operate between 15 and 50 mL/min, maintaining a pressure drop over the D2000 of less than 300 mm Hg. [22]

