**Abstract**

Objectives: This study aims to evaluate the safety, and 28-day mortality, associated with administering therapeutic plasma exchange (TPE) to adult patients with serious/life-threatening COVID-19 requiring intensive care unit admission

Trial design: Randomized, open-label, controlled, multicenter study. Subjects who will meet the enrollment criteria stated below and provide informed consent will be randomly allocated to the intervention group (TPE) or control (no TPE). Both groups will receive empiric COVID-19 treatment and ICU supportive care.

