**Timeline**

The recruitment phase will extend over a period of 6 months aiming on including at least 20 patients in the study group (TPE) and 20 controls (patients with severe COVID-19 who will undergo standard therapy per MOH, KSA protocol and who will provide consent only to share their clinical and laboratory data) per participating center. Starting date: 10-05-20.

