**Consent for TPE**

**Informed consent will be obtained in Arabic and English for this study.**

After obtaining informed consent, eligible patients who meet the inclusion criteria will undergo TPE sessions. As mentioned above the number of sessions will be individualized per clinical case scenario. Our preliminary experience is that patients with severe COVID-19 may require up to 5-7 sessions to improve.

Other supportive and therapeutic measures should continue according to the Saudi MOH approved protocols (Saudi Ministry of Health. Coronavirus Diseases 19 (COVID-19) guidelines. March 2020; version 1.2; (https://covid19.moh.gov.sa).

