**Study design**

We are aiming on a pilot prospective design of 6 months duration. We are aiming to include at least 20 adult patients with severe COVID-19 as per inclusion criteria in our study group (TPE arm) per participating center. At least 20 COVID-19 patients and/or their next of Kin who will only consent for sharing their clinical and laboratory data (they will be treated per standard MOH protocol) will serve as a control group to compare the efficacy of the intervention per participating center. Our primary specific aim of this pilot randomized controlled trial is to evaluate the safety of utilizing TPE in critically ill COVID-19 patients and 28 day mortality. At present our best estimate of this critically ill population's mortality is 50%. As COVID-19 is a novel virus and the global pandemic interventions will result in dynamic changes in incident rates of this infection, we will be enrolling a convenience of critically ill COVID-19 patients in order to inform us of an estimated mortality rate and variability of organ dysfunction in order to inform the sample size calculation of a definitive randomized controlled trial in the future. Consequently we are hoping to consent and randomize approximately 60 patients in each group over a 3 to 6 months period. The two groups will be receiving the same standard mechanical ventilation protocols (i.e., proning, ventilation strategies) as per hospital protocol. Antibiotics, antivirals, other medications and dialysis/CRRT will be applied between groups as per hospital and Saudi MOH protocols for treatment of patients with serious COVID-19 (Saudi Ministry of Health. Coronavirus Diseases 19 (COVID-19) guidelines. March 2020; version 1.2; (https://covid19.moh.gov.sa).

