**Secondary endpoints:**

Improvement of organ function as evaluated per SOFA score

Changes in laboratory inflammation markers

ICU length of stay

Number of days on mechanical ventilation

**Randomization** Eligible consented patients will be randomized after their stratification by ICU center and two PaO2/FIO2 ratio categories (> 150 and ≤ 150). Randomization will occur in variable block sizes of 4 to 8 patients. We will utilize a web-based randomization service, [randomize.net](http://randomize.net/) to allocate patients to their respective strata prior to the intervention or control therapy. Given the nature of the TPE technology, the intervention will be unblinded (open label); hence, no enrollment concealment will be expedited. However, the lack of allocation concealment will be mitigated as much as possible by the following measures. First, the primary outcome of mortality will not be disputable. Second, we have standardized co-interventions that impact on mortality as much as possible. These interventions include a) concomitant drug therapies for COVID-19, b) algorithms for mechanical ventilation including the early use of prone-ventilation, low tidal volume ventilation and neuromuscular blockade, c) the standard use of a broad spectrum antibiotic(s) for a minimum of 7 days to treat any potential superinfection be a bacterial pneumonia and d) standard criteria to initiate intermittent hemodialysis or CRRT such as hyperkalemia, profound metabolic acidosis, oliguria unresponsive to furosemide challenges of 1-1.5 mg/kg, e) the presence or development of coagulopathy defined as INR > 3.0 or Fibrinogen < 1.0 will be treated in a standard fashion in both the intervention and control group. We will define the date/time of appropriateness for ICU transfer irrespective of treatment allocation and recognizing that some COVID-19 patients randomized to the intervention group may improve to the point of appropriateness to transfer to the medical ward but requiring ICU care only to deliver remaining TPE doses as outlined in the protocol.

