**Data collection**

Clinical information of all enrolled cases will be retrieved from the hospital electronic/paper records system, including the: baseline demographic data, days of illness duration, presenting symptoms, radiological findings (CXR and Chest CT scans when possible), Sequential Organ Function Assessment (SOFA) and APACHE II scores. Data will be collected upon hospital/ICU admission, and prior to the first TPE session (Day 0) then on days 3, 7, 14, 30 accordingly and/or upon ICU/hospital discharge. Laboratory infectious marker testing results like culture from respiratory, urinary or blood culture will be collected accordingly.

Common laboratory and inflammatory markers (see below) will be collected on a daily basis:

1. CBC differential to include percent and absolute lymphocyte count and percent and absolute neutrophil count

2. Chemistry panel to include Total protein, Albumin, Lactate Dehydrogenase (LDH), Aminotransferases (ALT, AST), Procalcitonin

3. Cardiac biomarkers (e.g. cardiac troponins)

4. CK

5. Ferritin, LDH

6. Full coagulation profile to include PT, APTT, fibrinogen and D-dimer levels

7. C Reactive Protein (CRP) and erythrocyte sedimentation rate (ESR)

8. Interleukin-6

RT-PCR test for SARS-CoV-2 will be done and will be monitored during treatment and at day 14 of recovery or discharge, whatever is later. Also, we will be monitoring: mechanical ventilation (MV) and modes, intranasal oxygen inhalation, non-invasive mechanical ventilation, number of days of MV or nasal oxygen support, medication regimens (i.e., hydroxychloroquine, anti-viral therapies, steroids, tocilizumab, etc.), complications (including acute renal failure, acute coronary syndrome, myocarditis, acute respiratory distress syndrome, GI complications, CNS complications and nosocomial infections).

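### Tocilizumab, steroids and unnamed other drugs are withheld in the TPE arm, with no matching rule for controls, while COVID-19 drug therapy is described as standardised across arms

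*Protocol*

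**What the plan says.** **The restriction.** Under TPE mode and therapeutic considerations, the protocol notes that "It is well documented that TPE removes various medications i.e., monoclonal autoantibodies" and concludes that "use of Tocilizumab, steroids or other drugs as co-interventions will be not applied in our study group receiving TPE". The Timeline section uses the term study group for the TPE arm, so the sentence is about that arm.

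**Control care.** The Timeline section describes controls as "patients with severe COVID-19 who will undergo standard therapy per MOH, KSA protocol". Study design repeats that they follow the standard Ministry of Health (MOH) protocol. Neither section mentions a drug restriction.

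**Common care.** The Randomization paragraph, which follows the secondary endpoints, offers standardised co-interventions as one of two safeguards for the open-label design: "we have standardized co-interventions that impact on mortality as much as possible. These interventions include a) concomitant drug therapies for COVID-19". Study design says: "Antibiotics, antivirals, other medications and dialysis/CRRT will be applied between groups as per hospital and Saudi MOH protocols". The Abstract says: "Both groups will receive empiric COVID-19 treatment and ICU supportive care". Consent for TPE says: "Other supportive and therapeutic measures should continue according to the Saudi MOH approved protocols". None of these carries an exception for the drugs restricted in the TPE arm.

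**Recording.** Data collection lists, among the items monitored, "medication regimens (i.e., hydroxychloroquine, anti-viral therapies, steroids, tocilizumab, etc".

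**The concern.** An open-label trial of an add-on procedure isolates the effect of that procedure only if the rest of the care follows the same rule in both arms. Here one section plans a difference in drug treatment between the arms, and another relies on drug treatment being standardised.

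If controls receive drugs that TPE patients are denied, the 28-day mortality difference combines the effect of TPE with the effect of withholding those drugs. The mortality data alone cannot separate the two. This matters because 28-day mortality is a primary endpoint, and Study design says the pilot's mortality estimate is meant to inform the sample size of a definitive trial.

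The restriction also ends in a category that names no drug. Centres cannot tell which further drugs are excluded and may apply different rules to their TPE patients.

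**Working it through.** The protocol gives no figure on this point, so there is none to reproduce. The check is mainly textual, followed by a calculation for scale.

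**Text, side by side**

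1. *Which arm is restricted?* The TPE arm. The stated reason, removal of drugs by the exchange, cannot apply to a patient who is not exchanged.
2. *Is there a matching rule for controls?* No. Timeline and Study design refer control care to the MOH protocol without qualification.
3. *Is drug care described as common to both arms?* Yes. The clearest statements are item (a) of the Randomization list and the Study design sentence on medications. The Abstract and Consent for TPE point the same way but are weaker, because neither promises identical drugs.
4. *How wide is the restriction?* The last category is open. Consent for TPE, Study design and item (c) of the Randomization list (standard broad-spectrum antibiotics) make it implausible that all medication is barred. Which further COVID-19 drugs are barred is not stated.
5. *What is unaffected?* Items (b) to (e) of the Randomization list, and the first safeguard, that death as an outcome cannot be disputed.
6. *Can the analysis repair it?* Not simply. The models under Statistical analysis adjust for age, gender, admission PaO2/FIO2 ratio, APACHE II, SOFA, coagulopathy and CRS group, but not for co-medication. Adding it would not help: use arises after randomisation, and with none in the TPE arm the restriction and the arm coincide.

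**Scale, for illustration only**

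Inputs:
- Mortality of 50%, from Study design. The protocol does not say whether this figure includes use of the drugs, so both readings are shown.
- *u*, the share of controls who receive the drugs: assumed, 0 to 100%.
- *r*, the ratio of mortality with the drugs to mortality without them: assumed, 0.8 to 1.25.
- No use in the TPE arm and no TPE effect, so any difference is an artefact of the drug rule.

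Formulas for the difference, TPE minus control:
- Reading A, where 50% is control mortality with such use: 0.50 / (1 − *u*(1 − *r*)) − 0.50
- Reading B, where 50% is mortality without the drugs: 0.50 × *u* × (1 − *r*)

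Worked example at *u* = 0.5, *r* = 0.8:
- A: 0.50 / (1 − 0.5 × 0.2) − 0.50 = 0.5556 − 0.50 = +5.6 points
- B: 0.50 × 0.5 × 0.2 = +5.0 points

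All results, in percentage points:

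| Control use *u* | A, *r* = 0.8 | A, *r* = 1.25 | B, *r* = 0.8 | B, *r* = 1.25 |
|---|---|---|---|---|
| 0% | 0 | 0 | 0 | 0 |
| 25% | +2.6 | −2.9 | +2.5 | −3.1 |
| 50% | +5.6 | −5.6 | +5.0 | −6.3 |
| 100% | +12.5 | −10.0 | +10.0 | −12.5 |

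A positive value makes TPE look harmful and a negative value makes it look beneficial. The shift is also zero at *r* = 1.

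**The case against.** - **The one-arm reading rests on silence.** The sentence sits in a section on TPE dosing, which naturally discusses only patients on TPE. If COVID-19 drugs are standardised between arms, restraint in controls might be implied. That reading is possible but not compelled, because the stated reason is specific to TPE and control care is tied to the MOH protocol instead.
- **Whether the arms would differ in practice is unknown.** It depends on MOH and hospital protocols that are not in the document. If those do not call for the drugs, controls get none and there is no shift. This stands in full. Monitoring steroids and tocilizumab does not show that controls are meant to receive them.
- **The standardisation claim is qualified.** It extends only as far as possible, so the TPE rule could be a specific exception to a general statement. This softens the conflict without removing it. The qualifier covers practical shortfalls in delivering equal care, whereas this is a planned difference in the first item listed.
- **The calculation proves nothing about this trial.** Correct: both drug inputs are assumed, and the results straddle zero.
- **Differences between centres are minor for bias.** Randomisation is stratified by centre, so they add heterogeneity in the intervention rather than confounding by centre. This also stands.
- **Comparing two strategies is legitimate, especially in a pilot.** It is, provided it is declared. The Abstract presents TPE versus no TPE on common background treatment.

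**Conclusion.** The concern holds as a contradiction in the protocol's treatment rules and should be fixed. The TPE arm is denied named and unnamed drugs, controls have no matching rule, and the protocol still counts COVID-19 drug therapy among the standardised care that offsets the open-label design. Followed as written, this allows the 28-day mortality contrast to mix the effect of TPE with that of withheld drugs.

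Confidence is high for the textual conflict only. No actual imbalance is shown, and the protocol does not determine the size or direction of any bias. Within the assumed ranges the shift runs from zero to 12.5 points either way, with the extremes requiring use in every control.

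**What to change.** **Preferred.** Replace the open-ended category with a list of the restricted drugs, and apply one rule to both arms: allowed in both or barred in both. The choice is clinical.

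**If the rule must differ by arm:**
1. State in the aim and in the conclusion that two strategies are compared: TPE without the named drugs, and standard care that may include them.
2. Add an exception for the named drugs to item (a) of the Randomization list. Leave other COVID-19 drugs and items (b) to (e) as standardised.
3. Report use of the named drugs by arm beside the primary result, without adjusting for use after randomisation.

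**Cost.** A protocol amendment and a site memo. Steroid and tocilizumab use is already recorded, so no new data are needed for these. Each option has a drawback. Allowing the drugs in both arms accepts that TPE may remove part of the dose. Barring them in both may depart from the MOH standard care promised to controls. Keeping the rule different narrows the conclusion to a comparison of strategies.

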**Consent for TPE**

**Informed consent will be obtained in Arabic and English for this study.**

After obtaining informed consent, eligible patients who meet the inclusion criteria will undergo TPE sessions. As mentioned above the number of sessions will be individualized per clinical case scenario. Our preliminary experience is that patients with severe COVID-19 may require up to 5-7 sessions to improve.

Other supportive and therapeutic measures should continue according to the Saudi MOH approved protocols (Saudi Ministry of Health. Coronavirus Diseases 19 (COVID-19) guidelines. March 2020; version 1.2; (https://covid19.moh.gov.sa).

**Study design**

We are aiming on a pilot prospective design of 6 months duration. We are aiming to include at least 20 adult patients with severe COVID-19 as per inclusion criteria in our study group (TPE arm) per participating center. At least 20 COVID-19 patients and/or their next of Kin who will only consent for sharing their clinical and laboratory data (they will be treated per standard MOH protocol) will serve as a control group to compare the efficacy of the intervention per participating center. Our primary specific aim of this pilot randomized controlled trial is to evaluate the safety of utilizing TPE in critically ill COVID-19 patients and 28 day mortality. At present our best estimate of this critically ill population's mortality is 50%. As COVID-19 is a novel virus and the global pandemic interventions will result in dynamic changes in incident rates of this infection, we will be enrolling a convenience of critically ill COVID-19 patients in order to inform us of an estimated mortality rate and variability of organ dysfunction in order to inform the sample size calculation of a definitive randomized controlled trial in the future. Consequently we are hoping to consent and randomize approximately 60 patients in each group over a 3 to 6 months period. The two groups will be receiving the same standard mechanical ventilation protocols (i.e., proning, ventilation strategies) as per hospital protocol. Antibiotics, antivirals, other medications and dialysis/CRRT will be applied between groups as per hospital and Saudi MOH protocols for treatment of patients with serious COVID-19 (Saudi Ministry of Health. Coronavirus Diseases 19 (COVID-19) guidelines. March 2020; version 1.2; (https://covid19.moh.gov.sa).

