**Methodology**

This will be a multicenter pilot prospective clinical study evaluating the potential efficacy of TPE recruiting convenience sample of patients with severe COVID-19 who may present with ARF/ARDS, sepsis, MSOF and CRS. The primary site will be King Saud Medical City (KSMC), Riyadh, Kingdom of Saudi Arabia (KSA). Also, the study will run in ICUs (MOH Health Cluster 1; Riyadh) and other centers in KSA pending their IRB approval.

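### The protocol gives two incompatible rules for how a patient becomes a control: randomisation after consent, or consent to data sharing only

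*Protocol*

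**What the plan says.** Two descriptions of allocation run through the protocol.

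**Consent, then randomise.** The Abstract says that subjects who meet the criteria and "provide informed consent will be randomly allocated to the intervention group (TPE) or control (no TPE"). The Randomization paragraph, which follows the list of secondary endpoints, says "Eligible consented patients will be randomized after their stratification by ICU center and two PaO2/FIO2 ratio categories" and adds "Randomization will occur in variable block sizes of 4 to 8 patients", using a web-based service. Study design calls the study a pilot randomised controlled trial and hopes to consent and randomise about 60 patients in each group.

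**Type of consent goes with the arm.** Of certain patients or next of kin, the same Study design section says that they "will only consent for sharing their clinical and laboratory data (they will be treated per standard MOH protocol) will serve as a control group". Timeline describes the controls in the same way, as patients on standard therapy "who will provide consent only to share their clinical and laboratory data". Consent for TPE says "After obtaining informed consent, eligible patients who meet the inclusion criteria will undergo TPE sessions" and goes on to the number of sessions without mentioning allocation.

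**The concern.** Under the first description, every control has accepted the possibility of TPE before the arm is known. Under the second, a control has agreed to data sharing and nothing more, so has not agreed to be randomised. Read literally, Consent for TPE leaves no consenting eligible patient who could become a control.

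28-day mortality is a primary endpoint, and the case for comparing it between arms rests on randomisation. A site that works from Timeline and Consent for TPE could treat those who agree to TPE and count the others as controls. The protocol says elsewhere (Therapeutic options for COVID-19) that TPE is already being given empirically, so that route would be familiar.

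The measures in the Randomization paragraph that are meant to offset open-label treatment are an indisputable outcome and standardised co-interventions. Neither deals with selection into the arms. The Cox and logistic models adjust for seven covariates: age, gender, PaO2/FIO2 ratio, APACHE II, SOFA, coagulopathy and CRS group. They would not remove selection on anything unmeasured.

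**Working it through.** **Step 1: compare the texts.**

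| Protocol section | What the patient consents to | What sets the arm |
|---|---|---|
| Abstract | The trial | Random allocation |
| Randomization | The trial, before allocation | Stratified blocks, web service |
| Study design (later sentences) | The trial | Randomisation, about 60 per group |
| Study design (control sentence) | Data sharing only | Membership of the data-only group |
| Timeline | Data sharing only (controls) | As above |
| Consent for TPE | TPE | Consent plus eligibility |

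A person cannot both have consented only to data sharing and have consented to randomisation with TPE as a possible result. Consent sought after allocation could in principle fit a data-only control, but no section describes it, and the Abstract and Randomization both put consent first.

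**Step 2: what is at stake if the consent wording is followed.** The protocol's 60 per group comes with no effect size or power, so there is no stated calculation to reproduce. The check below asks how often a trial with no TPE effect would give p<0.05 if the two groups differed in baseline risk.

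Inputs from the protocol: n = 60 per group and mortality of 50% (Study design); two-sided 0.05 and a chi-square test (Statistical analysis). Assumed, because the documents give no figure: a baseline mortality gap g, split evenly around 50%, so p1 = 0.5 + g/2 and p2 = 0.5 − g/2.

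With a and b deaths in the two groups and pooled proportion p̄ = (a + b)/(2n):

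Z = [(a − b)/n] / √[p̄(1 − p̄) × 2/n]

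P(p<0.05) = Σ Bin(a; n, p1) × Bin(b; n, p2), summed over all (a, b) with |Z| > 1.96.

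| Assumed gap | Mortality in the two groups | 60 per group | 20 per group |
|---|---|---|---|
| 0 points | 50% / 50% | 5.5% | 4.3% |
| 5 points | 52.5% / 47.5% | 9.2% | 5.3% |
| 10 points | 55% / 45% | 20.6% | 8.4% |
| 15 points | 57.5% / 42.5% | 39.3% | 14.0% |
| 20 points | 60% / 40% | 61.2% | 22.2% |

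The 20-per-group column uses the protocol's minimum for one centre. The results are symmetric. If the controls are the sicker group, nearly all the excess is a false benefit of TPE (at 10 points and 60 per group, 20.5 of the 20.6 percentage points). If they are the healthier group, it is a false harm.

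Rough check by hand for the 10-point gap: the standard error is √(2 × 0.25/60) = 0.0913, so the gap is 0.10/0.0913 = 1.10 standard errors, and 1 − Φ(1.96 − 1.10) is about 19%, close to the exact 20.6%.

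**The case against.** The strongest reply is that randomisation is the only allocation procedure the protocol specifies. The Randomization paragraph gives strata, block sizes and a service, and Study design speaks of randomising patients in each group, which includes the controls. On this view the data-only sentences loosely describe what a control undergoes, namely standard care plus data collection, and Consent for TPE covers only the TPE arm. Nowhere does the protocol say that those who refuse TPE become controls.

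Part of this stands. A reader might infer that the trial is in fact non-randomised, and the documents do not support that. They support a contradiction whose effect depends on which text a site follows. A reader might also take the Methodology phrase "recruiting convenience sample of patients with severe COVID-19" as further evidence. It is not, because a convenience sample concerns who enters the trial and can still be randomised. Nor can one conclude that controls will in practice sign a form that omits randomisation, since the consent form is not available to check.

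The benign reading itself does not stand. In both Timeline and Study design the word 'only' limits the consent given, not the procedures undergone, and no section offers the softer meaning.

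**Conclusion.** The protocol contains an unresolved contradiction about consent and allocation, and it should be corrected before patients are enrolled on it, because a wrong consent or a non-random arm cannot be repaired in the analysis. This is a matter for the protocol and consent form, and a statistical analysis plan could not settle it.

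The consequence is conditional. Where sites follow the Abstract and Randomization, the comparison is randomised. Where they follow the data-only and TPE-consent wording, it is observational. In that case, with no true effect and 60 per group, the false-positive rate would be about 9% to 61% for assumed gaps of 5 to 20 points, against 5.5% with no gap.

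Those gaps are assumptions and the direction is unknown. A reader might infer a bias in favour of TPE of some particular size, but the documents give no basis for either the sign or the amount.

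**What to change.** Bring Timeline, Study design and Consent for TPE into line with the Abstract and Randomization:

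- Use one consent, obtained before allocation from the patient or next of kin, that covers randomisation to TPE or no TPE and the use of data.
- Remove the definition of controls as people who consent to data sharing alone from Timeline and Study design. Define them as patients randomised to no TPE.
- Reword Consent for TPE so that it is patients randomised to TPE who go on to the sessions.
- State that those who decline randomisation are not analysed as trial controls.

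The cost is a protocol and consent-form amendment through the IRB. Some people who would have shared data only may decline to be randomised, which could slow recruitment. The target of about 60 per group does not change.
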